#### Costs

For cost-effectiveness analyses, two questionnaires are used to investigate healthcare resources utilisation and patient costs. The Five-level EQ-5D (EQ-5D-5L) is a short and widely used questionnaire in both clinical and health-economic research as its scores can easily be translated into quality adjusted life years (QALYs), the primary outcome measure for most cost-effectiveness research [30, 31]. It consists of five questions on domains of HRQoL, such as mobility, pain, and daily functioning. In addition, patients’ and healthcare costs and costs with regard to productivity losses will be assessed with a subset of questions from the Institute for Medical Technology Assessment (iMTA) Productivity Cost Questionnaire (iPCQ) and the iMTA Medical Cost Questionnaire (iMCQ) [32, 33].

#### Decisional regret

Decisional regret regarding the choice for CC or dialysis, will be determined with the validated Decisional Regret Scale [36]. Multiple studies assessed the regret of patients to start dialysis with results ranging from 7.4% in a Dutch survey up to 61% in a Canadian study [43–46]. Currently, there is a lack of data regarding the decisional regret comparing CC with dialysis. An additional questionnaire (Treatment Choice & Decisional Conflict Scale) regarding the treatment choice made will be added to gain more insight in the decision-making process regarding the choice between CC and dialysis [34, 35].

### Outcome variables

The primary outcome parameter is HRQoL (Table 2). DIALOGICA will assess three secondary outcome parameters: clinical outcomes, cost-effectiveness, and decisional regret. The clinical outcomes that will be assessed are mortality, hospitalisation, functional status, cognitive functioning, and frailty. All outcomes are assessed with (repeated) measures during the first year of the second stage.

**Table 2 Tab2:** Study outcomes

Outcomes			Instruments
Primary outcome	HRQoL		SF-12 physical and mental component scores [28]
Secondary outcomes	Clinical outcomes	Mortality (all-cause)	ERA-EDTA codes [16, 47]
		Hospitalisation (all-cause)	ICD-10 codes [48]
		Functional status	Katz-ADL [14], Lawton-iADL [15]
		Cognitive functioning	MoCA [17], 6-CIT [18], LDST [20]
		Frailty	Clinical Frailty Scale [25]
	Cost-effectiveness		ICERs, calculated using EQ-5D-5 L [30] and iPCQ/iMCQ [32, 33]
	Decisional regret		Decisional Regret Scale [36]

All outcomes are repeated measures during the first year of the second stage (Fig. 1)

*Abbreviations*: *6-CIT* six-item Cognitive Impairment Test, *EQ-5D-5L* Five-level EQ-5D, *ERA-EDTA* European Renal Association - European Dialysis & Transplant Organisation, *HRQoL* Health-Related Quality of Life, *(i) ADL* (Instrumental) Activities of Daily Living, *ICD-10* International Statistical Classification of Diseases, 10th edition, *ICER* Incremental Cost-Effectiveness Ratio, *iMCQ* iMTA Medical Costs Questionnaire, *iPCQ* iMTA Productivity Cost Questionnaire, *LDST* Letter-Digit Substitution Test, *MoCA* Montreal Cognitive Assessment, *QALY* Quality Adjusted Life Year, *SF-12* Twelve-item Short Form Health Survey

#### HRQoL

HRQoL is assessed by comparing repeated measurements of both the calculated Physical Component Summary Score and the Mental Component Summary Score of the SF-12 at the start of the second stage and after 3, 6 and 12 months after the start of the second stage.

#### Clinical outcomes

Mortality will be analysed as all-cause mortality within the first year of the second stage. The cause of death will also be categorised into seven categories, based on the United Kingdom Renal Registry, using ERA-EDTA codes (Table S2) [16, 47]. Hospitalisation will be analysed as all-cause hospitalisation within the first year of the second stage and each individual episode will be categorised into seven categories, using ICD-10 codes (Table S3) [48]. Functional status, cognitive functioning, and frailty will be repeated measures (at the start of the second stage and after 12 months) using their respective instruments, described in the previous paragraphs.

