## Background

In the Netherlands, over 6200 patients (358 per million population) with kidney failure are currently dependent on dialysis with an annual incidence of over 1650 patients (95 per million population) [1]. The proportion of older patients has risen over the years and in 2019 45% of the incident dialysis patients were 70 years or older [2]. After dialysis initiation, the overall mortality in this age group is high: 18% in the first year, 72% after 5 years [2]. A Dutch retrospective single-centre study showed no survival benefit from dialysis initiation for patients aged 80 years or older and in those above 70 years with severe comorbidity, compared to conservative care (CC) [3]. These results were confirmed by a prospective multicentre study performed in the Netherlands [4]. Results such as these have shifted the focus from mortality towards health-related quality of life (HRQoL) as the most important outcome [5]. Dialysis is associated with a high treatment burden in older patients when compared to CC [6, 7]. A recent meta-analysis reviewed 11 studies comparing HRQoL between older patients treated with CC or dialysis [7]. All studies had a small sample size, eight were single-centre, and eight were highly susceptible to selection bias and/or confounding. Thus, current evidence for the effects of CC or dialysis on HRQoL is both limited and biased. Despite these limitations, the authors conclude that CC has the potential to achieve similar HRQoL as dialysis.

Outcomes such as survival and HRQoL might differ greatly among older patients with kidney failure due to substantial heterogeneity with respect to functional and cognitive impairment and frailty. Establishing which of these conditions are associated with poor outcome may help to identify those patients at highest risk and thus guide informed treatment decisions [8]. To do this, some authors suggest tailoring the comprehensive geriatric assessments used in geriatric care to routine kidney failure care [9]. However, studies showing the benefit of these assessments on outcomes, such as survival and HRQoL, in these patients are lacking.

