**Fig. 1 Fig1:**
[figure not shown]
Study flow chart. Abbreviations: *eGFR* estimated Glomerular Filtration Rate, *HRQoL* Health-Related Quality of Life, *NGA* NephroGeriatric Assessment

DIALOGICA is aimed to run for a total of 4 years with a minimum follow-up of 1 year in the second stage. The study is conducted according to the principles of the Declaration of Helsinki and the ICH-GCP guidelines. Primary ethical approval was obtained from the medical research ethics committee of the The Hague region (METC Zuidwest Holland) on May 24th 2019 (reference number 19–071). Local medical research ethics committees in participating centres will also be asked for local ethical approval. The study is registered in the Netherlands Trial Register under NL-8352.

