### Data registration

At baseline, all relevant demographical and clinical data will be collected. In the first stage of the study, a follow-up visit will be scheduled once-yearly until the start of the second stage. In the second stage, data collection will be performed at start, after 3 months, 6 months, 12 months, and thereafter annually until end of follow-up or end of the study. All data will be recorded in a database developed in collaboration with Nefrovisie. Nefrovisie is the Dutch Quality Institute for Nephrology which hosts the Renine-database, in which all Dutch patients on kidney replacement therapy are registered. Upon consent, data for DIALOGICA will be linked to the Renine-database and the databases of three Dutch studies with similar or complementary study aims and outcomes: the *Dutch nOcturnal and hoME dialysis Study To Improve Clinical Outcomes* (DOMESTICO) study will compare HRQoL, clinical outcomes and costs in home dialysis patients with in-centre haemodialysis patients; the *Pathway for OLDer patients with End-stage Renal disease* (POLDER) project will assess the feasibility of implementing a geriatric assessment in routine predialysis care for older patients with an eGFR < 20 mL/min/1.73m^2^ and the *Optimizing Access Surgery In Senior haemodialysis patients* (OASIS) study will compare three strategies of vascular access in older patients using a randomised design [11–13]. The DIALOGICA database will be archived for future research during a minimum of 15 years after the completion of this study.

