## Discussion

With an ageing population with kidney failure, more patients will face the decisional moment whether to start dialysis or not. As the survival benefit of dialysis treatment in the geriatric population is debatable, focus has shifted towards HRQoL as primary outcome measure. The impact of dialysis on HRQoL of older patients is probably large, but current data comparing it to CC are both limited and biased, creating an urgent need for high-quality studies [7]. DIALOGICA will be the first large study to prospectively assess the differences between patients choosing CC or dialysis. With a total follow-up of up to 4 years, outcome parameters can be assessed in more detail. Biological age, which also takes factors such as functional status, cognitive functioning, and somatic functioning into account, might influence these outcomes more than calendar age. This study will help to determine individual patient characteristics to identify patients less likely to benefit from dialysis initiation. This will support patients with kidney failure and their nephrologists in making a well-informed and shared decision when discussing renal replacement therapy. To do so, DIALOGICA combines a practical test set of well-validated questionnaires and assessments that can be performed in less than 1 hour per patient. With better identification of patients who might not benefit from dialysis, a significant reduction in costs for treatment of kidney failure can be achieved if these patients choose for CC, since CC has far lower annual treatment costs compared to dialysis [6].

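### One-year mortality is the only mortality outcome although stage-2 follow-up continues beyond it; an added analysis over all follow-up would gain about 50 to 127 deaths from data already collected

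*Protocol article*

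**What the plan says.** Under Clinical outcomes the article fixes the horizon: "Mortality will be analysed as all-cause mortality within the first year of the second stage". The Outcome variables section applies the same limit generally: "All outcomes are assessed with (repeated) measures during the first year of the second stage". The Abstract and the footnote to Table 2 repeat it.

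Other sections describe longer follow-up. Study design says: "DIALOGICA is aimed to run for a total of 4 years with a minimum follow-up of 1 year in the second stage". One year in stage 2 is therefore the minimum. Data registration schedules stage-2 visits at the start and "after 3 months, 6 months, 12 months, and thereafter annually until end of follow-up or end of the study". The Discussion adds: "With a total follow-up of up to 4 years, outcome parameters can be assessed in more detail".

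The Statistical analysis section plans Kaplan-Meier curves and a Cox model for mortality and hospitalisation and names no time horizon. The Background gives the only mortality figures: "After dialysis initiation, the overall mortality in this age group is high: 18% in the first year, 72% after 5 years". The article states no mortality for conservative care, no accrual pattern, and no event target or power for mortality.

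**The concern.** The stated outcomes and the stated follow-up do not fit together. If every outcome closes at 12 months, no defined outcome uses stage-2 follow-up after month 12, although the visits take place and the Discussion counts the longer follow-up as a benefit. Kaplan-Meier and Cox methods accommodate unequal follow-up, so a common one-year minimum does not require the only mortality analysis to stop there.

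Two things are at stake. The first is precision. The study hypothesis is that conservative care has comparable clinical outcomes in subgroups of older patients. A first-year comparison with few deaths, fewer still within subgroups, can easily show no significant difference, and a reader could take that as support. The second is scope: a one-year window cannot show a survival difference that emerges later.

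**Working it through.** **Plan's own figure.** The article sizes the study on the SF-12 only. With a difference of 3.0, SD 9.0, two-sided alpha 0.05, 80% power and a 1:4 ratio, the conservative-care group needs 1.25 × (9 × 2.80 / 3)² ≈ 88.3, so 89, and dialysis needs 353.2, so 354. The total is 443. Dividing by 0.90 gives 99 + 394 = 493. Both totals reproduce. There is no mortality figure to reproduce.

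**Inputs.** From the article: N = 493 (99 conservative care, 394 dialysis); death proportions of 18% at 1 year and 72% at 5 years; stage-2 follow-up of at least 1 year in a 4-year study. Assumed: dialysis mortality in both groups, a constant hazard from year 1 to year 5, and follow-up patterns between 1 and 4 years.

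**Survival curve.**
- After year 1 the hazard is h = ln(0.82 / 0.28) / 4 = 0.269 per year, or annual survival of 0.764.
- For follow-up uniform from 1 to b years, the expected death proportion is 1 − 0.82 × [1 − exp(−h(b − 1))] / [h(b − 1)].

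**Deaths.**
- First year only: 0.18 × 493 = 88.7, about 89. In conservative care, 0.18 × 99 = 17.8, about 18.
- Follow-up 1 to 2 years: 1 − 0.82 × 0.877 = 0.281, giving about 138 deaths.
- Follow-up 1 to 4 years: 1 − 0.82 × 0.687 = 0.437, giving about 215 deaths.

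If enrolment is spread over 2 to 3 years and progression to stage 2 occurs at a constant rate of one third in 3 years, the same curve gives about 189 to 181 deaths with N held at 493.

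**Precision (Schoenfeld).** SE(log HR) = 1 / √(0.2 × 0.8 × deaths); the HR detectable with 80% power is exp(2.80 × SE).

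| Analysis | Deaths | SE(log HR) | 95% CI factor | Detectable HR | Power at HR 1.5 | Deaths after year 1 |
|---|---|---|---|---|---|---|
| First year | 89 | 0.265 | 1.68 | 2.10 | 33% | none counted |
| All, 1 to 2 years | 138 | 0.212 | 1.52 | 1.81 | 48% | 36% |
| All, enrolment over 2 to 3 years | 189 to 181 | 0.182 to 0.186 | 1.43 to 1.44 | 1.66 to 1.68 | 61% to 59% | 53% to 51% |
| All, 1 to 4 years | 215 | 0.170 | 1.40 | 1.61 | 66% | 59% |

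An observed HR of 1.0 in the first-year analysis would have a 95% confidence interval of about 0.60 to 1.68. The gain from all follow-up is 138.5 − 88.7 ≈ 50 to 215.4 − 88.7 ≈ 127 deaths.

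**Sensitivity.** If the conservative-care hazard is 3 times that on dialysis, the share of deaths after year 1 is 33% with follow-up of 1 to 2 years and 54% with 1 to 4 years. A constant 18% per year, which ignores the article's 72%, gives 30% and 53%. With 443 patients, the first-year analysis has about 80 deaths and a detectable HR of 2.19.

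**The case against.** The strongest case for the plan is that one year is a deliberate and legitimate horizon. It is stated consistently, equals the minimum stage-2 follow-up, gives every patient the same window whatever the entry date, and matches the horizon of the primary outcome. Mortality is a secondary outcome in a study that says attention has moved from survival to quality of life, and no power is claimed for it. All of this stands, and it is a reason to keep the one-year outcome.

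A reader might infer that most deaths are being thrown away. The documents do not support that. The 72% figure is at 5 years, beyond the study's 4-year span, and describes patients after dialysis initiation only. The 4 years also include stage 1, so follow-up uniform over 1 to 4 years in stage 2 is an optimistic case. The share of deaths after year 1 may be near a third. Nor are the later data discarded: annual collection continues, the Kaplan-Meier and Cox text sets no horizon, and nothing forbids a longer analysis. The Discussion sentence covers total follow-up across both stages, so it fits poorly with the outcome definitions without flatly contradicting them.

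It is also fair that longer follow-up does not cure the low precision, much of which comes from about 493 patients split 1:4. Stage 2 can begin without dialysis once eGFR reaches 10 or below, so longer follow-up also leaves more time for treatment changes and non-proportional hazards.

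What survives is narrower. The article does define the mortality outcome, and it defines only one. Leaving a longer analysis to be chosen later gives up the benefit of prespecifying it.

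**Conclusion.** The point holds as a cheap improvement. It does not show that the one-year outcome is wrong or should be replaced. The only defined mortality outcome stops at 12 months while stage-2 data collection goes on. On the stated assumptions, the first-year comparison is imprecise: about 89 deaths and 80% power only for an HR of about 2.1. All available follow-up would raise the deaths to between 138 and 215 and lower the detectable HR to about 1.8 to 1.6.

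These sizes rest on 493 patients reaching stage 2, a 1:4 split, dialysis mortality in both groups and an assumed accrual pattern. The article does not give the last two, so the share of deaths after year 1 can only be put at roughly a third to three fifths. Power at an HR of 1.5 rises from 33% to between 48% and 66%, still below 80%. A non-significant result should not be read as evidence of comparable survival under either analysis.

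**What to change.** - Keep all-cause mortality within the first stage-2 year as stated.
- Add a prespecified analysis of time from stage-2 start to death over all available follow-up, administratively censored at end of study, using the Kaplan-Meier and Cox methods already planned.
- Amend the Clinical outcomes text, the general sentence in Outcome variables and the Table 2 footnote so that mortality is no longer limited to the first year. The Discussion sentence on 4-year follow-up then has a defined outcome behind it.
- Show numbers at risk, report a proportional-hazards check, and state how changes of treatment during stage 2 are handled.
- Report the hazard ratio with its confidence interval, and do not treat non-significance as comparability.

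The cost is a few lines of wording and one analysis, with no new data collection. The downside is that late follow-up is carried by early entrants, and a longer window allows more treatment changes and non-proportional hazards. Hence the numbers at risk and the check.

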#### Cost-effectiveness

QALYs will be calculated using the EQ-5D-5L [30]. Total healthcare costs will be calculated using a subset of questions from the iPCQ and iMCQ [32, 33]. Cost-effectiveness will be assessed as total costs per QALY using incremental cost-effectiveness ratio’s (ICERs).

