### Nephrogeriatric assessment

To assess the most common geriatric domains (i.e. functional, psychological, somatic, and social status) and the study’s outcome measures (i.e. HRQoL, clinical outcomes, and costs), a geriatric assessment tailored to the kidney failure population will be used. It is derived from the consensus-based test set used in a pilot study [11]. This nephrogeriatric assessment (NGA) consists of a combination of 12 questionnaires and seven tests and assessments (Table 1). Nine questionnaires are answered independently by the patient at home and three are conducted by an interviewer. All of the tests and assessments are performed in the participating centres. The NGA is performed at baseline and at a yearly interval during the first stage. Upon entering the second stage, a new NGA will be performed, repeated again at yearly intervals. The questionnaires on HRQoL, symptoms and costs are also repeated after 3 and 6 months into the second stage. To minimise inter-observer bias, the tests will be performed by trained geriatric or (pre) dialysis nurses only.

**Table 1 Tab1:** The nephrogeriatric assessment used in DIALOGICA

Domain	Measure	Type	Explanation	Scale / cut-off
Functional status	Activities of Daily Living (Katz) [14]	SAQ	Grading of dependency on 6 functions, e.g. bathing, dressing.	0–12, higher scores indicating more dependency, no cut-off values.
	Instrumental Activities of Daily Living (Lawton) [15]	SAQ	Grading of dependency on 8 more complex functions, e.g. handling finances, driving.	0–8 for women, 0–5 for men. Higher scores indicating more independency, no cut-off values.
	Fall risk assessment	IAQ	One-year history of falling and graded fear of falling.	Yes/no; 1 (‘no fear’) to 10 (‘very afraid’).
	Hand grip strength	T	Measured using a Jamar handheld dynamometer, 3 repetitive measurements for both hands.	Highest measurement is used for analysis. Individual cut-off values based on age and gender [16].
Psychological status	Montreal Cognitive Assessment (MoCA) [17]	T	Screening tool for cognitive impairment in 8 domains (visuospatial, naming, memory, attention, language, abstraction, delayed recall, orientation).	0–30, higher scores indicating better cognitive performance, < 26 indication of cognitive impairment.

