	Dialysis Symptom Index (DSI) [29]	SAQ	30 Questions regarding presence of specific symptoms, when present scored on a 5-point Likert scale. Used in Dutch nephrological care as PRO.	Yes/no, if yes 1 (‘not at all’) to 5 (‘very much’). Total score 0–30 for each ‘yes’, higher scores indicating higher number of symptoms. No cut-off values.
Costs	Five-level EQ-5D (EQ-5D-5L) [30]	SAQ	5 Questions regarding health aspects (mobility, self-care, usual activities, pain/discomfort, anxiety/depression) using a 5-point Likert scale and 1 overall health score on a visual-analogue scale. Used to calculate QALYs in cost-effectiveness analysis	1 (‘no problems’) to 5 (‘unable to/extreme problems’); 0 ‘worst health you can imagine’ to 100 (‘the best health you can imagine’ for the visual-analogue scale. Reference values using Dutch value set [31].
	(subset of questions from) iMTA Productivity & Medical Costs Questionnaire [32, 33]	SAQ	8 General questions and 22 questions on healthcare use in the previous 3 months. Used to calculate healthcare-related costs in cost-effectiveness analysis.	NA
Decisional regret	Treatment Choice Questionnaire & Decisional Conflict Scale (DCS) [34, 35]	SAQ	Questionnaire filled in when treatment choice has been made. Contains 23 questions regarding the choice made.	NA for Treatment Choice Questionnaire; 0–100 for DCS, higher scores indicating higher decisional conflict, no cut-off values.
	Decision Regret Scale (DRS) [36]	SAQ	5 Questions on regret regarding the choice for either conservative care or dialysis on a 5-point Likert scale.	0–25, higher scores indicating stronger feelings of regret. No cut-off or reference values [37].

*Abbreviations*: *CA* Clinician Assessment, *HRQoL* Health-Related Quality of Life, *IAQ* Interviewer-Administered Questionnaire, *iMTA* Institute for Medical Technology Assessment, *PRO* Patient Reported Outcome, *SAQ* Self-Administered Questionnaire, *T* Test, *NA* Not Applicable, *QALY* Quality Adjusted Life Year

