### Statistical analysis

All statistical analyses will be performed using statistical software, such as SPSS and R. Univariable and multivariable regression analysis to correct for possible confounders will be used to compare groups. Longitudinal data will be analysed with linear and logistic mixed models and presented as estimated coefficients and odds ratios with 95% confidence intervals. Cumulative incidence of hospitalisation and mortality will be reported in Kaplan Meier curves. A Cox proportional hazards model will be used to compare the rate of mortality and hospitalisation between groups. Overall costs and ICERs will be compared across the two groups using linear regression. Discounting, a mathematical procedure for adjusting future costs to their ‘present day value’, will be applied, as requested for all health economic evaluation exceeding a time frame of 1 year. To deal with missing data, multiple imputation by fully conditional specification will be applied.

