DIALOGICA has an observational study design instead of a randomised controlled design. We deemed the patient’s choice between CC and dialysis too fundamentally different to let it be determined by fate. Randomised studies for treatment modalities have been shown to be challenging in patients with kidney failure in general as they have large and different implications for patients’ daily life. For example, a previous Dutch study that tried to randomise patients between haemodialysis and peritoneal dialysis failed and the choice whether or not to start dialysis arguably has even more impact [50]. To our knowledge, only one study comparing CC and dialysis is currently recruiting patients using a randomised design [51]. The implication of the observational design of DIALOGICA is that it is more sensitive to confounding by indication, since observed and unobserved variables can influence outcome of treatment. However, selective inclusion into randomised controlled studies can also lead to poor external validity of their results and an observational study may provide a better reflection of daily clinical practice. To account for the influence of the observed variables on treatment outcome and thus to limit confounding by indication, extensive correction for confounding will be applied, using a large set of patients’ characteristics.

Treating physicians and patients are not blinded for the results of the NGA, because this could hamper appropriate care for newly diagnosed geriatric impairments. Moreover, as NGAs are becoming standard of care in most Dutch centres, it is ethically undesirable to withhold the results of the NGA from treating physicians and participating patients. Since the results of the NGA might influence the treatment decision both for patients and for treating physicians this can introduce selection bias between patients choosing for CC and dialysis, and could be considered a limitation. Where needed, correction for baseline NGA discrepancies will be applied.

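### The plan regresses ICERs on treatment group, which cannot be done; the QALY increment has no model of its own, and adjustment for starting EQ-5D utility is left conditional

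*Protocol article*

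**What the plan says.** The Cost-effectiveness section defines the ingredients: "QALYs will be calculated using the EQ-5D-5L" and "Total healthcare costs will be calculated using a subset of questions from the iPCQ and iMCQ". The result is to be expressed as an ICER, in cost per QALY.

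The only sentence in Statistical analysis that addresses the economic comparison is "Overall costs and ICERs will be compared across the two groups using linear regression". QALYs are not named there.

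Adjustment is promised elsewhere. Statistical analysis says "Univariable and multivariable regression analysis to correct for possible confounders will be used to compare groups". The Discussion says "extensive correction for confounding will be applied, using a large set of patients’ characteristics", and adds that differences in the baseline NGA will be corrected for if necessary.

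The data for adjustment are collected. Table 1 lists the EQ-5D-5L and the cost form, with "22 questions on healthcare use in the previous 3 months", as NGA instruments. A new NGA is done on entry to the second stage, and "The questionnaires on HRQoL, symptoms and costs are also repeated after 3 and 6 months into the second stage".

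**The concern.** Two things go wrong together.

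First, the named analysis does not exist as written. A regression needs one outcome value per patient. Each patient has a cost and a QALY total, but an ICER arises only once both between-group differences have been estimated. The sentence therefore gives a model for the numerator and none for the denominator, so the promised confounder correction has no stated QALY regression to act through.

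Second, a QALY total built from repeated utilities normally includes the starting utility. The groups are formed by patient choice, and the Discussion itself acknowledges confounding by indication and the influence of NGA results on that choice. If the groups start at different utilities, part of the gap stays in the QALY difference unless the model removes it. When the QALY difference is small, a small residue changes the ICER considerably. Cost-effectiveness is one of the three named secondary outcomes, and lower cost is part of the study hypothesis.

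**Working it through.** **The plan's own figures.** No figure is stated for cost-effectiveness, so there is none to reproduce. The group sizes used below come from the Sample size calculation, which does reproduce: 1.25 × (9 × (1.960 + 0.842) / 3)² = 88.3, so 89 on conservative care; 4 × 88.3 = 353.2, so 354 on dialysis; divided by 0.9 these give 99 and 394.

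**Why an ICER cannot be regressed on group.** ICER = (mean cost on dialysis − mean cost on conservative care) / (mean QALY on dialysis − mean QALY on conservative care). The group contrast is already inside the ratio, so nothing is left to compare across groups.

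**How much of a starting gap enters the QALY difference.** The document gives no rule for turning utilities into QALYs. I assume the trapezoidal rule at 0, 3, 6 and 12 months, with all patients alive through the year. The weights are:

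- start: 0.25 / 2 = 0.125
- 3 months: 0.50 / 2 = 0.25
- 6 months: (1 − 0.25) / 2 = 0.375
- 12 months: 0.50 / 2 = 0.25

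They sum to 1. With starting gap d, of which a fraction r persists at every later visit, the shift is d × (0.125 + 0.875 r). The gaps are assumed values:

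| Starting gap d | r = 0 | r = 0.5 | r = 1 |
|---|---|---|---|
| 0.02 | 0.0025 | 0.011 | 0.020 |
| 0.05 | 0.006 | 0.028 | 0.050 |
| 0.10 | 0.0125 | 0.056 | 0.100 |

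Deaths during the year would shrink the part that works through persistence.

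**Against sampling error.** With an assumed QALY SD of 0.25, SE = 0.25 × √(1/99 + 1/394) = 0.028. For SDs of 0.20 and 0.30 it is 0.022 and 0.034. At an SD of 0.25, the three shifts for d = 0.05 are about 0.2, 1.0 and 1.8 standard errors.

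**Effect on the ICER.** Assume a true gain of 0.10 QALY and an incremental cost of EUR 50,000, so the ICER is EUR 500,000 per QALY. A 0.05 gap with half persisting gives 50,000 / (0.10 + 0.028) ≈ EUR 390,000 or 50,000 / (0.10 − 0.028) ≈ EUR 696,000, depending on which group starts higher.

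**Where the promised adjustment reaches.** The conditional clause concerns the baseline NGA. The Data registration and Nephrogeriatric assessment sections use that word for study entry, and distinguish it from the new NGA done on entering the second stage. The clause may therefore refer to an assessment made well before the outcome year begins, and it does not clearly secure utility at the start of the second stage.

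**The case against.** The best reply is that adjustment is promised. Multivariable correction applies to group comparisons in general and could be read to cover QALYs. Both instruments belong to the NGA. An article may leave its covariate list to a fuller document, and not even the primary outcome has one here. The sentence on ICERs may simply be shorthand.

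Much of this stands, and it rules out several stronger readings that a reader might infer:

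- **That there is no adjustment.** The Statistical analysis section and the Discussion say otherwise.
- **That any starting imbalance passes wholly into the ICER.** Under the trapezoidal rule only 12.5% of a utility gap enters mechanically; the rest depends on how much of the gap persists.
- **That earlier costs leak into the cost total.** The form at the start of the second stage looks back 3 months, before the outcome year. Those costs matter only as a predictor.
- **That the ICER would change sign.** This needs a very small true gain and a gap in one particular direction. The document gives neither, and its expectation of comparable HRQoL is limited to subgroups.

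The reply does not rescue the printed sentence. A missing covariate list can be left to another document, but the article names an analysis that cannot be run and does not name the QALY comparison. Nor does the reply make adjustment for starting utility unconditional.

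**Conclusion.** The point holds as a defect in stated text: ICERs cannot be compared across groups by linear regression, the QALY increment has no model of its own, and control of starting utility hangs on a conditional clause that may refer to study entry.

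The consequence is a possible residual bias in the QALY difference, not a demonstrated one. For a starting gap of 0.05 it ranges from 0.006 to 0.05 QALY, against a standard error of about 0.028. The gap, its persistence, the SD and the trapezoidal rule are all assumptions, and the direction is unknown. The point concerns a secondary outcome and leaves the primary analysis untouched.

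**What to change.** Replace the sentence on costs and ICERs with the following:

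- Regress one-year costs and one-year QALYs separately on treatment group, both with the confounder set.
- Always include EQ-5D utility at the start of the second stage in the QALY model. If that form was completed after dialysis began, use the last pre-dialysis value.
- Include prior 3-month cost as a predictor in the cost model.
- Form the ICER or net benefit from the two adjusted increments, with their joint uncertainty, for example by bootstrapping patients through both models.

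This needs new wording and a little more analysis work, with no new data collection. One limitation remains: first-stage assessments are yearly, so for some patients the last pre-dialysis utility may be up to about a year old. A cost form of that age would not cover the 3 months before the second stage.
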